## Methods

### Research design & participant population

#### Research design

This parallel, double-blind randomized controlled trial, that is 52-weeks in lengths, will randomly assign 200 mCSPC survivors receiving ADT to Cr + RT or PLA + RT with randomization in blocks of size four (two randomized to Cr + RT and two randomized to PLA + RT within each consecutive group of four subjects), stratified by age (< 70 years vs. ≥ 70 years) and ECOG performance status (0,1,2). To preserve the blind, only the Investigational Drug Services Pharmacy (IDS) personnel, the Research Compliance Office, and the Data Safety Monitoring Committee at Huntsman Cancer Institute (HCI) will know treatment assignments. Access to unblinded data/documents will be controlled by the pharmacy to ensure the blind is maintained. In the case of an emergency, [name] (mPIs) and the participant’s treating medical oncologist have the sole responsibility for determining if unblinding of a participant’s treatment assignment is warranted. If unblinding is warranted, the investigator will contact IDS for treatment assignment.

At baseline, completion of 24- and 52-weeks (end-of-study), we will assess muscle mass, fatigue, physical function, independence, insulin sensitivity, fat mass, and quality of life, and collect plasma for cell-free DNA analysis. We will also extract standard of care Prostate-Specific Antigen measurements from the medical record at these time points. All participants will be instructed to continue their typical diet and medication regimens. Figure 2 provides a schematic of the study design, intervention, and assessment time points. This study was approved by the University of Utah Institutional Review Board (IRB_00168125). The trial was registered in ClinicalTrials.gov (NCT06112990) on November 2, 2023 and is currently open to enrollment. Protocol amendments will be made as needed following standard procedures.

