### Statistical analysis

With respect to the primary outcome, we anticipate at least a 2 kg difference between intervention arms (Cr + RT vs. PLA + RT) in baseline to 52 week change in muscle mass based on sustaining, or more likely extending, differences seen in a supervised trial conducted by Chrusch and colleagues [56]. In this trial, 30 older men (mean age 70 + years) were randomized to Cr + RT vs. PLA + RT, and body composition and strength endpoints were compared at 12 weeks [56]. In the creatine arm, the men gained an average of 3.3 kg in muscle mass, while in the placebo arm, the men gained 1.3 kg, corresponding to a 2 kg difference in lean mass change over 12 weeks.

Muscle mass values within individuals are expected to be strongly correlated (after adjusting for time by treatment arm). In Chrusch and colleagues [56] study, repeated measurements of muscle mass over a short time interval, and without an intervening treatment, had an intra-subject correlation of 0.99. At each time point, the standard deviation of muscle mass was approximately 5.8. In our 12-week pilot study, we found a standard deviation of muscle mass of 8.24 kg with an intra-subject correlation between baseline and 12-week measurements of 0.975. We might realistically expect intra-subject correlation (ICC) of at least 0.85, given intervening treatment with RT and potentially creatine as well as a 52-week follow-up period. For a sample size of 200 (100 per arm), if the ICC is 0.85, then the power will be ∼ 84% for a mean difference of 2 kg muscle mass change.

The primary analyses will be conducted from a modified intention-to-treat perspective, with each subject analyzed according to their randomized study arm, irrespective of participation or compliance, as long as they complete their baseline assessments. Changes in muscle mass from baseline to 52-weeks will be compared between the Cr + RT and PLA + RT arms in the context of a linear mixed effects model, based on each subject’s measurements at baseline 24-weeks and 52-weeks, with a random effect for subject, and fixed effects for time, study arm, study arm by time interaction, and a priori anticipated important drivers of changes in muscle mass (age, length of time on ADT, ECOG performance status) at randomization. The effect estimate, and associated Wald test, of the study arm at 52 weeks corresponds to the estimate of the intervention effect (Cr + RT vs. PLA + RT), and its associated hypothesis test.

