A few additional analyses are pre-planned to add robustness and clarity of interpretation. One suite of additional analyses will omit the 24-week follow-up measurements from the primary analysis model. Additional analyses will also be conducted omitting the anticipated drivers of responsiveness to intervention from the collection of adjustment variables. Lastly, we plan to conduct a suite a subgroup analyses, accompanied by subgroup by intervention arm interaction tests, for subgroups defined by age, length of time on ADT, baseline muscle mass, RT compliance (≥ 80% of scheduled sessions vs. <80%), and supplement compliance within the Cr + RT arm (≥ 80% of prescribed dose consumed vs. < 80%). Within the Cr + RT arm, compliance to creatine supplementation protocol will be summarized as percentage of prescribed doses overall and by phase (loading vs. maintenance phase), and changes in muscle mass from baseline to 52 and 24-weeks summarized separately for compliance groups (≥ 80% of prescribed dose vs. <80%, and ≥ 80% of scheduled sessions vs. <80%).

Analyses will assume that data is missing-at-random (MAR; data values are independent of the missing data mechanism conditional on the observed data), the most general data-centric missing data assumption [57]. Missing outcome data (e.g. muscle mass) will handled by simply omitting those observations from the mixed effects model, which is valid under MAR. Missing data on covariates (e.g., age, length of time on ADT, and ECOG performance status) will be handled via multiple imputation, which also ensures validity under MAR [58].

Notably, follow-up measurements missing due to patient death will not be MAR, and follow-up measurements missing due to severe declines in patient health may not be MAR either. Throughout, estimates for differences in baseline to follow-up changes in endpoints between the study arms will be conditional on the subset of patients who would have been able to continue on study procedures. While we do not anticipate enough overall survival or progression-free survival events for well-powered comparisons, these endpoints will be compared between study arms in supplemental analyses. Additionally, while we expect both study arms to provide benefits to our patients, the study will be under continuous oversight of an independent Data Safety Monitoring Committee at HCI, which will be monitoring for risks to patients.

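### Effect modification by three continuous variables (age, time on ADT, baseline muscle mass) is described only through subgroup-by-arm tests, which lose information if modification is roughly linear

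*Protocol article*

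**What the plan says.** The additional analyses in the Statistical analysis section include "subgroup analyses, accompanied by subgroup by intervention arm interaction tests", for "subgroups defined by age, length of time on ADT, baseline muscle mass" and for two compliance measures. The compliance measures come with explicit cuts, for example "RT compliance (≥ 80% of scheduled sessions vs. <80" per cent. For age, time on ADT and baseline muscle mass the article gives no cut-point, number of groups or split rule. The only age cut in the document is in Research design, where randomization is "stratified by age (< 70 years vs. ≥ 70 years) and ECOG performance status (0,1,2" as the levels; it is not tied to the subgroup analysis.

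In the primary model, age and time on ADT enter as adjustment terms, described as "a priori anticipated important drivers of changes in muscle mass (age, length of time on ADT, ECOG performance status) at randomization". No term there lets the treatment effect vary with them. That model is "based on each subject’s measurements at baseline 24-weeks and 52-weeks", so baseline muscle mass is one of its responses.

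**The concern.** These analyses are meant to show which men gain more from creatine. The variable interacted with arm is the subgroup, and making a subgroup from a continuous variable requires grouping it. Men just either side of a cut are then treated as different, and men far apart on the same side as alike. When modification is gradual, this weakens a test that has limited power at this sample size, and the answer can move with the cut. A true gradient could be reported as no evidence of a difference between subgroups.

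For baseline muscle mass there is also a question of model form. The variable that defines the subgroup is a response in the mixed model, whereas a baseline-by-arm question fits more naturally in a model of the follow-up value adjusted for baseline.

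**Working it through.** **Inputs.** From Statistical analysis: 200 men, 100 per arm; SD of muscle mass 8.24 kg (12-week pilot); intra-subject correlation 0.85. Assumed: two-sided 5% test. The size of any effect modification and the shape of each modifier's distribution are not in the article, so ranges are shown.

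**The plan's own figure.** The article gives no power for interaction tests. Its figure of about 84% is for the 2 kg main effect. SD of change = 8.24 × √(2 × 0.15) = 4.51 kg. Main-effect power = Φ(2 / [4.513 × √(2/100)] − 1.960) = Φ(3.133 − 1.960) = 0.88. A value of 0.844 appears with 90 per arm, that is, with attrition the article does not state. The stated figure is lower than the recomputed one, and the difference has no bearing on this point. Only the SD of change is carried forward.

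**Step 1: information kept after grouping.** For a linear interaction, the efficiency of a grouped test relative to a continuous one is the squared correlation between the variable and its grouped form. For a normal variable cut at proportion p this is φ(z_p)² / [p(1 − p)]. At the median: 0.3989² / 0.25 = 0.637 = 2/π, a loss of 36%; 200 × 0.637 = 127 men's worth of information.

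| Modifier and grouping | Loss |
|---|---|
| Normal, quartiles (scored by group mean) | 14% |
| Normal, tertiles (scored by group mean) | 21% |
| Uniform, median split | 25% |
| Normal, median split | 36% |
| Normal, 30/70 split | 42% |
| Lognormal (sigma 0.5), median split | 48% |
| Normal, 20/80 split | 51% |
| Exponential, median split | 52% |

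For age cut at 70 with an assumed SD of 8 years, the loss is 36% if the mean age is 70, 42% if it is 66 or 74, and 56% if it is 62 or 78.

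**Step 2: what this does to power.** The standard error of the continuous interaction is 4.513 × √(4/200) = 0.638 kg per SD of the modifier. Power of 80% needs (1.960 + 0.842) × 0.638 = 1.79 kg per SD. After a median split: Φ(2.802 × √0.637 − 1.960) = Φ(0.275) = 0.61. A 4,000-run simulation gave 78% and 60%. A separate 6,000-run simulation at 1.8 kg per SD gave about 79% continuous, 60% median split, 56% for 70/30 and 48% for 80/20. With no modification, rejection was 5.5% (continuous) and 5.3% (median split).

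**Step 3: smaller modification.** At 1.0 kg per SD, 1.0/0.638 = 1.567. Continuous power is Φ(1.567 − 1.960) = 0.35; median-split power is Φ(1.567 × 0.798 − 1.960) = 0.24. At 0.5 kg per SD the two are 12% and 10%.

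**Step 4: threshold modification.** With an effect of 0 below the median and 3.6 kg above it, simulation gave 79% for the median split and 59% for the continuous test. The ranking reverses.

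**Step 5: baseline muscle mass.** With SD 8.24, correlation 0.85 and 1.8 kg per SD, a median split tested on change had 64% power. A continuous baseline-by-arm term in a baseline-adjusted model of the 52-week value had 82%. Both held about 5% type I error. With a uniform 2 kg effect, the median split on change rejected 4.9% of the time with a bias of 0.01 kg.

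**The case against.** The strongest reply is that grouping is inferred. The article gives no cuts for these three variables, it does not rule out a continuous test alongside the subgroups, and such coding is normally settled in a full protocol or analysis plan that is not shown. Part of this stands: the absence of cut-points is not a fault of the article, and no single loss figure can be attributed to the plan. But the test the article names is a subgroup-by-arm test, and specifying the cuts later would not turn it into a continuous one.

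A reader might infer that a third of the information is always lost, or that any cut loses power. Neither is supported. The 36% figure needs a normal modifier, a single median split and linear modification, and under a threshold the split does better. The 1.8 kg per SD used for illustration is also large: around a mean effect of 2 kg it implies 2 − 1.8 = 0.2 kg at one SD below the mean and 2 + 1.8 = 3.8 kg at one SD above. With smaller modification both tests are weak, and the absolute power gap shrinks.

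A reader might also infer that using baseline muscle mass both as subgroup and as response biases the comparison. It does not: regression to the mean acts equally in both randomized arms and cancels in the contrast. What remains there is efficiency and coherence.

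Finally, these are additional analyses, and subgroups with interaction tests are common practice. That limits the weight of the point, but the remedy is correspondingly cheap.

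**Conclusion.** The point holds as a low-cost improvement to the additional analyses, not as an error in the trial's main inference. The article describes only grouped tests of modification for three continuous variables. If modification is roughly linear, the information lost runs from about 14% (quartiles of a normal modifier) through about 36% (median split of a normal modifier) to over 50% (a strongly skewed modifier or a very unbalanced cut), and the result depends on the cut. These figures rest on assumed distributions and on linearity; the article supplies neither. Type I error stays near 5%, no bias is shown, and the primary estimate, its test and the sample size do not change.

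**What to change.** State that the main test of effect modification treats each variable as continuous:

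- Age and time on ADT: a covariate-by-arm-by-time term in the planned mixed model, read at 52 weeks.
- Baseline muscle mass: a baseline-by-arm term in a model of the 52-week value adjusted for baseline. The reason is efficiency and coherence, not removal of bias.
- Planned subgroup estimates: keep them for display, using the 70-year randomization cut for age.
- Linearity: check with a spline, and compare the fitted trend with the subgroup estimates.

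The cost is one or two sentences and no new data. The downside is that the continuous test assumes a roughly linear trend and can have less power than a split if the true modification is a threshold. The spline and the displayed subgroups are there to reveal that.

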## Discussion

The Creatine-52 trial aims to identify the most effective solution to address the needs of mCSPC survivors receiving ADT. Findings from this trial will build upon previous work from the investigative team, where we demonstrated safety, feasibility, and efficacy of 12-weeks of Cr + RT compared with RT alone to be superior in preserving muscle mass, improving fatigue, physical function, and whole-body strength (NCT03987217). This will be the first study, to our knowledge, to assess longer-term (e.g., 52-weeks) efficacy of Cr + RT compared with PLA + RT on changes in muscle mass, health outcomes, and quality of life; which is important because longer-term solutions that address needs of mCSPC survivors are needed. Furthermore, a current gap in our knowledge is the efficacy of long-term engagement in RT and creatine monohydrate supplementation use in this patient population to improve health outcomes.

Additionally, this approach addresses a major facilitator to RT among mCSPC survivors, implementation of home-based programs [24, 25, 59], while utilizing a supervised model for safety. This approach is translational as it can be adopted by cancer centers nationwide who use an established telemedicine system. Findings from this trial will also improve delivery of comprehensive survivorship care by providing a multicomponent, patient-centered lifestyle strategy to preserve muscle mass, improve health outcomes and quality of life, and complement cancer treatment in this patient population. This patient-centered strategy can be translated on a large-scale because creatine monohydrate supplementation and elastic resistance bands are inexpensive and widely available. Further, our findings will lead to simple recommendations that the oncology care team can provide in clinic (e.g., “Take 5 grams of creatine monohydrate daily, and engage in an RT program twice per week”). If the hospital does not have an associated exercise oncology program, the provider can instruct the patient to consult the American College of Sports Medicine’s Moving Through Cancer Exercise and Rehabilitation program directory to find a local program that fits the patient’s needs [60].

Development of this trial was not only informed by the 12-week trial carried out by the investigative team, but also in coordination with the Salt Lake City Community Prostate Cancer Support Group. Individuals from this group helped the investigative team refine the intervention and assessment procedures. This group will continue to partner with the investigative team throughout the duration of the project by attending bi-annual investigative team meetings. Examples of input provided by the community group include inquiry of space needs at assessment sessions for RT program delivery, and submission of weekly supplementation logs for accountability.

In summary, this trial aims to test a patient-centered approach to a problem of high priority within survivorship care of individuals living with mCSPC. More research related to supportive care interventions in the metastatic setting are needed considering the growing prevalence of individuals living with metastatic cancer [61]. This work also aligns with the most recent NCI Cancer Moonshot priority which is to “improve the experience of people and their families living with and surviving cancer” [62].

## Data Availability

No datasets were generated or analysed during the current study.

## Abbreviations

ADL: Activity of Daily Living
ADT: Androgen Deprivation Therapy
ARUP: Associated Regional University Pathologists
cfDNA: cell-free DNA
Cr: Creatine monohydrate supplementation
Cr + RT: Creatine monohydrate + Resistance Training
DSMC: Data Safety Monitoring Committee
PLA + RT: Placebo + Resistance Training
POWER: Personal Optimism With Exercise Recovery
PROMIS: Patient Reported Outcomes Measurement Information System
PSA: Prostate Specific Antigen
QoL: Quality of Life
RT: Resistance Training
SOC: Standard of Care
DXA: Dual-energy X-ray Absorptiometry
ECOG: Eastern Cooperative Oncology Group
FACIT-Fatigue: Functional Assessment of Chronic Illness Therapy- Fatigue questionnaire
FACT-P: Functional Assessment of Cancer Therapy-Prostate questionnaire
FDA: Food and Drug Administration
HCI: Huntsman Cancer Institute
HIPAA: Health Insurance Portability and Accountability Act
HOMA-IR: Homeostatic Model Assessment for Insulin Resistance
ICC: Intra-subject Correlation Coefficient
IDS: Investigational Drug Services
mCSPC: Metastatic Castration Sensitive Prostate Cancer
MAR: Missing At Random
PLA: Placebo
